### Allocation and blinding

Infants will be randomly allocated to the active monitoring or abduction treatment group. Randomization will be performed by a computer-generated randomization schedule. Block randomization will be used, stratifying for Graf type IIa-/IIb/IIc and participating center. Due to the nature of this study, parents/caregivers and treating physicians cannot be blinded. However, the researchers performing the data analyses will be blinded.

### Data collection methods

Data collection is embedded in standard-care follow-up moments according to the Dutch DDH guideline (Table 3) [17]. At the enrollment consultation, baseline patient characteristics, physical examination data, and ultrasonographic measurements will be collected by the physician or researcher. Infants and parents/caregivers will return for a consultation at the orthopedic department every six weeks (± 1 week) to collect physical examination data, ultrasonographic measurements, and data on compliance and complications, until one of the endpoints (Table 2).

Additionally, baseline cost- and HRQoL questionnaires will be sent to the parents/caregivers via email. One parent/caregiver is asked to digitally fill in the cost- and HRQoL questionnaires at baseline and after 3, 12, and 18 months. The parent/caregiver will fill in two HRQoL questionnaires, one for the infant and one for the parent/caregiver. If the parent/caregiver has not filled in the questionnaires, a digital reminder will be sent after two weeks, and the parent/caregiver will be contacted by phone after four weeks.

At the age of 12 and 24 months (± 1 month), the infants and parents/caregivers will return for a consultation at the orthopedic department to collect physical examination data, radiograph measurements, and data on complications.

All members of the TRAM-Trial team will be protocol trained for standardized evaluation of included subjects.

### Data management

A data management plan was constructed. All data will be pseudonymized prior to entry into the Castor database (Castor, Amsterdam, the Netherlands). The local principal investigators and research nurses in the participating centers have access to the local code key. Two PhD-students have access to the code key of all participating centers. Source documents will be stored locally at the participating centers. All ultrasounds and radiographs will be pseudonymized and stored at MUMC + . The local principal investigators and research nurses in the centers will have access to local source documents. The two PhD-students, monitors, and the Health and Youth Care Inspectorate will have access to all source documents. All data will be stored for 15 years.

### Statistical methods

Statistical analyses will be performed according to the intention-to-treat principle and per-protocol approach. The difference in rate of normal hips between active monitoring and abduction treatment at the age of 12 and 24 months will be analyzed with chi-square tests. The non-inferiority margin will be set to 10% and non-inferiority will be demonstrated if one side of the 95% confidence interval lies outside the non-inferiority margin.

A Kaplan Meyer analysis will be performed to study the time to hip normalization, with events defined as Graf I or acetabular index lower than 25 degrees at 12 months or acetabular index lower than 25 degrees at 24 months. Differences in survival curves will be studied and tested for statistical significance with the Log Rank test. The relation between patient characteristics and the rate of normal hips at the age of 12 and 24 months will be studied with prediction models. Using backward elimination, a multivariable cox regression model will be constructed. The Receiver Operating Characteristic (ROC) curve and Area Under the Curve (AUC) will be used as performance parameters, goodness-of-fit will be determined by inspection and publication of the calibration plot and publication of discrimination parameters, and internal validation of the model will be performed with bootstrapping. Compliance will be presented using descriptive analysis. The difference in the number of complications will be studied with a t-test (total number of complications) and chi-square test (number of infants with a complication). Differences in quality of life and parent/caregiver satisfaction will be determined with generalized estimated equations (GEE). The statistical analyses will be performed with SPSS version 25 (IBM SPSS Statistics for Windows; Armonk, New York: IBM Corp.).

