## Methods/design

### Trial design and study setting

This is a multicenter, parallel-group, open-label, non-inferiority randomized controlled trial studying the (cost-)effectiveness of active monitoring versus abduction treatment for infants with centered DDH in fourteen hospitals in the Netherlands (Amphia Hospital, Amsterdam University Medical Center, Erasmus Medical Center, HagaZiekenhuis, Leiden University Medical Center, Maastricht University Medical Center, Máxima Medical Center, Medisch Spectrum Twente, Noordwest Ziekenhuisgroep, Onze Lieve Vrouwe Gasthuis, Reinier Haga Orthopedic Center, Sint Maartenskliniek, Spaarne Gasthuis, and University Medical Center Groningen). As part of the Dutch national DDH screening program, youth healthcare professionals will refer at-risk infants for an ultrasound evaluation at the age of three months (or sooner in case of suspected dislocation) [17]. Infants will be identified and recruited after diagnosis at outpatient clinics of the participating orthopedic departments. After diagnosis and assessment of the eligibility criteria, parents/caregivers will receive the written patient information leaflet. Parents/caregivers will return for a standard-care consultation to sign the informed consent after a reflection period of seven days. After written informed consent has been obtained, randomization and baseline measurements will be performed. Infants will be followed up until the age of 24 months.

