### Outcomes

#### Primary outcome

The primary outcome is the rate of normal hips, defined as an acetabular index lower than 25 degrees on an antero-posterior radiograph, at the age of 12 months.

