#### Secondary outcomes

The rate of normal hips, defined as acetabular index lower than 25 degrees on an antero-posterior radiograph, at the age of 24 months will be studied. Also, the relation between baseline patient characteristics and the rate of normal hips will be explored. Included patient characteristics are gender, birthweight, initial alpha angle, initial beta angle, laterality (right or left, unilateral or bilateral), history of DDH in relatives, breech presentation, swaddling, twin birth, parents/caregivers’ education level, ethnicity, range of abduction in flexion (degrees), and whether the child is the firstborn child of the parents/caregivers. Accordingly, the time to hip normalization is studied. Complications during the follow-up period will be examined. The compliance of wearing the abduction device in the abduction treatment group will be assessed using visual inspection of the abduction device and a parent/caregiver-question on the number of hours that the abduction device has been worn in the last 24 hours. Furthermore, resource use and costs will be assessed using standardized cost-questionnaires. The health-related quality of life (HRQoL) of the infant will be measured with the Visual Analogue Scale (EQ-VAS) of the youth version of the EQ-5D (EQ-5D-Y) and the Infant and Toddler Quality of Life Questionnaire Short Form (ITQOL-SF47), filled out by one parent/caregiver. Last, the HRQoL of one parent/caregiver will be measured with the EQ-5D-5L and parent/caregiver satisfaction with the treatment process will be assessed with the Visual Analogue Scale.

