### Sample size and recruitment

We hypothesize that the rate of normal hips of infants treated with active monitoring is not lower than the rate of normal hips of infants treated with an abduction device. Based on the study results of Ömeroglu et al. [18], we assume a rate of normal hips of 80%. The inferiority margin was set to 10%, based on consensus in the study group (70% adequate treatment in the active monitoring group, 80% adequate treatment in the abduction treatment group). With an alpha of 0.05 and power of 90%, the sample size is 370 infants per group. Accounting for 10% lost to follow up, a total of 800 infants (400 per group) is warranted.

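### The primary comparison is named as an unadjusted chi-square test, which is not linked to the confidence-interval non-inferiority rule and leaves out the stratification factors, Graf type and centre

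*Protocol article*

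**What the plan says.** The trial is described under Trial design and study setting as a "multicenter, parallel-group, open-label, non-inferiority randomized controlled trial". The outcome is binary: "The primary outcome is the rate of normal hips, defined as an acetabular index lower than 25 degrees on an antero-posterior radiograph", assessed at 12 months and, as a secondary outcome, at 24 months.

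Three statements bear on the primary analysis:

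- Statistical methods names the test. The difference in rates "at the age of 12 and 24 months will be analyzed with chi-square tests". No covariate or stratification factor is mentioned.
- The next sentence of that section gives the criterion: "non-inferiority will be demonstrated if one side of the 95% confidence interval lies outside the non-inferiority margin", with the margin at 10%. The section also asks for intention-to-treat and per-protocol analyses.
- Allocation and blinding describes the randomisation: "Block randomization will be used, stratifying for Graf type IIa-/IIb/IIc and participating center".

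Baseline alpha angle is collected and listed under Secondary outcomes ("Included patient characteristics are gender, birthweight, initial alpha angle, initial beta angle, laterality"). There it serves to relate baseline characteristics to the rate of normal hips.

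**The concern.** Two things do not fit together.

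First, the named test and the objective address different hypotheses. A chi-square test asks whether the two rates are equal. The trial asks whether active monitoring is worse by 10 points or more. The interval in the next sentence answers that question, but the text does not say that this interval is the primary analysis or how the chi-square result relates to it. A report could therefore carry two answers to the primary question.

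Second, the randomisation balances the arms within Graf type and centre, and the named analysis then ignores both. If these factors predict a normal hip, the unadjusted standard error is larger than it needs to be. In a non-inferiority trial a wider interval lowers the chance of meeting the criterion when the treatments are in truth equivalent.

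**Working it through.** **Inputs.** From Sample size and recruitment: normal-hip rate 80%; margin 10 points ("The inferiority margin was set to 10%, based on consensus in the study group"), so 70% v 80% at the margin; alpha 0.05; power 90%; 370 per group; 400 per group randomised with 10% loss, which leaves 400 × 0.9 = 360 evaluable. A two-sided 95% interval corresponds to one-sided 0.025. Assumed, because the document does not give them: the Graf mix, rates by Graf type, between-centre variation, and the share of outcome variance explained by covariates.

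**Step 1: which hypothesis the sample size serves.**

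- Non-inferiority, null variance at 80%/70% and alternative variance at 80%/80%: (1.96 × √0.37 + 1.2816 × √0.32)² / 0.10² = 367.5, so 368 per group. This is close to the stated 370.
- Equality test of 80% v 70%, two-sided: (1.96 × √(2 × 0.75 × 0.25) + 1.2816 × √0.37)² / 0.10² = 392 per group.
- The simpler non-inferiority formula, with variance at 80%/80% throughout, gives 337. Multiplied by 1.1 this is 371, but that would already include dropout.

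The stated size fits a non-inferiority calculation better than the chi-square comparison.

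**Step 2: whether test and interval can say different things.** Take 370 per group with 296/370 = 80.0% normal under abduction. For the chi-square, z = d / √(2p̄(1 − p̄)/n). For the Wald interval, the lower limit is d − 1.96 × √(p₁(1 − p₁)/n + p₂(1 − p₂)/n).

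| Normal under active monitoring | Difference (points) | Chi-square p | Lower 95% limit (points) |
|---|---|---|---|
| 274/370 | −5.95 | 0.0545 | −11.99 |
| 281/370 | −4.05 | 0.1833 | −10.02 |
| 282/370 | −3.78 | 0.2133 | −9.74 |

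From 274 to 281 the chi-square is non-significant while the lower limit is below −10 points, so non-inferiority is not shown. The two analyses are not interchangeable, and the plan should say which one is primary.

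**Step 3: precision lost by ignoring the strata alone.** This is a simulation with 4000 runs, 360 per group, and 42 strata (3 Graf types × 14 centres), using a Mantel-Haenszel risk difference with Sato variance. The assumed Graf mix is 30/50/20%.

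| Assumed rates by Graf type; centre SD (logit) | Power, unadjusted v stratified | Type I error at the margin, unadjusted v stratified | Mean SE at equal rates, unadjusted v stratified |
|---|---|---|---|
| 85/80/72%; 0.3 | 0.913 v 0.919 | 0.029 v 0.028 | 0.0300 v 0.0297 |
| 92/80/60%; 0.5 | 0.911 v 0.931 | 0.019 v 0.025 | 0.0304 v 0.0287 |

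The gain is about 0.6 to 2 points of power. Type I error is not materially inflated without stratification. In the second scenario the unadjusted analysis is somewhat conservative.

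**Step 4: precision with strata plus alpha angle.** At 80%/80% and 360 per group, the unadjusted SE is √(0.32/360) = 0.0298. The half-width is 1.96 × 0.0298 = 5.84 points, and power is Φ(0.10/0.0298 − 1.96) = 91.8%. If covariates explain a share R² of outcome variance, the SE is multiplied by √(1 − R²):

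| Assumed R² | Half-width (points) | Power |
|---|---|---|
| 0 | 5.84 | 91.8% |
| 0.05 | 5.70 | 93.1% |
| 0.10 | 5.54 | 94.2% |
| 0.15 | 5.39 | 95.3% |

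The gain is 1.3 to 3.5 points. As a cross-check, the stronger scenario of step 3 implies R² = 1 − (0.0287/0.0304)², about 0.11, for the strata alone. The 15% row therefore needs a further contribution from alpha angle.

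**The case against.** The strongest reply is that the criterion is already an interval against a margin. A reader might infer that the trial will be decided by a test of equality in place of a non-inferiority assessment. The article does not support that: the sentence after the named test sets the interval rule, the hypothesis is stated as non-inferiority, and the sample size fits it. A reader might also want to attach a false-claim rate to reading a non-significant chi-square as non-inferiority. No section proposes that reading, so no such rate can be charged to this plan.

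Nor is it right that alpha angle goes unused. It is listed among the characteristics to be related to the rate of normal hips, and Statistical methods describes prediction models for that relation. It is only not named for the primary comparison. Table 1 also defines Graf type partly by alpha angle (50–59 for IIa- and IIb, 43–49 for IIc), so the two overlap and adding alpha angle is optional.

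The unadjusted comparison after stratified randomisation is valid and, by the interval rule, already has 91.8% power at 360 per group, above the planned 90%. The gain is therefore extra precision and does not repair a shortfall.

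Finally, the interval method, covariate list and pooling of small centres may stand in an analysis plan that is not shown, and their absence is not the point here. What stands is that the article itself names a method, and the method named is unadjusted and is not tied to the stated criterion. The loose wording of the interval rule is a separate matter and adds no weight to this one.

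**Conclusion.** The point holds in a limited form. The chi-square test is mismatched to the primary question and unconnected to the interval rule that decides it, and it omits the factors by which the trial randomises. Validity is not threatened.

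The loss is about 0.6 to 2 points of power for the strata alone, and about 1 to 3.5 points if strata and alpha angle explain 5 to 15% of outcome variance. Both ranges rest on assumed heterogeneity that the document does not give; with weak predictors the gain would be close to nil. The mismatch between test and criterion does not depend on these assumptions. The change is worth making because it costs almost nothing and settles which result answers the primary question.

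**What to change.** Replace the chi-square as primary analysis with the following:

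- **Effect measure:** risk difference in normal hips at 12 months, active monitoring minus abduction, with a two-sided 95% confidence interval.
- **Stratification or adjustment:** Graf type and centre, with baseline alpha angle as an option. Either a Mantel-Haenszel risk difference or a standardised risk difference from logistic regression would serve.
- **Small centres:** a pooling rule fixed in advance. With 720 evaluable infants over 42 strata, the average is only about 17 per stratum (720/42).
- **Criterion:** non-inferiority is shown if the lower limit lies above −10 points, assessed in both the intention-to-treat and per-protocol sets.
- **24 months:** the same method.
- **Chi-square:** descriptive at most for these endpoints.

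The cost is a few sentences in the protocol or analysis plan and a few lines of code. Graf type, centre and alpha angle are already recorded. The choice should be fixed before outcome data by arm are seen, so that adjustment cannot be selected after the result is known.

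### The only stated non-inferiority rule, read literally, is the reverse of a valid criterion: it counts a confidence limit outside the margin as success

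*Protocol article*

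**What the plan says.** The decision rule appears once, in Statistical methods: "non-inferiority will be demonstrated if one side of the 95% confidence interval lies outside the non-inferiority margin". The sentence before it plans a comparison of the rate of normal hips between the two arms at 12 and 24 months.

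The direction of the trial is set elsewhere. Sample size and recruitment states: "We hypothesize that the rate of normal hips of infants treated with active monitoring is not lower than the rate of normal hips" in the abduction arm. On the margin it says "The inferiority margin was set to 10%, based on consensus in the study group", and it spells out the boundary in brackets: "70% adequate treatment in the active monitoring group, 80% adequate treatment in the abduction treatment group". The Discussion repeats that active monitoring should not yield a lower proportion of normal hips and calls the trial a non-inferiority study. The primary outcome is a rate of normal hips, so higher is better.

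**The concern.** With a favourable outcome and a 10-point margin, non-inferiority is shown when the data exclude a deficit of 10 points or more. The lower limit of the interval for active monitoring minus abduction must then stay above -10. If that limit lies beyond -10, a deficit larger than the margin has not been ruled out. The sentence in Statistical methods assigns success to that second pattern. It also speaks of one side of the interval without saying which.

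This sentence settles the primary conclusion of an 800-infant, open-label trial meant to inform usual care. If its key word has to be reversed before it can be used, the reader must rely on inference for the one rule that should be fixed in advance. A later dispute over what was prespecified could not be resolved from the text.

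**Working it through.** **Inputs.** From Sample size and recruitment: 80% normal hips assumed, margin 10 points, boundary 70% against 80%, alpha 0.05, power 90%, 370 per group, 400 per group recruited, 10% loss. From Statistical methods: a 95% confidence interval. Analysed per arm: 400 × 0.9 = 360.

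**The plan's own figure.** The article states "With an alpha of 0.05 and power of 90%, the sample size is 370 infants per group" and does not name the formula.
- Usual non-inferiority formula, one-sided 0.025, both arms at 80%: (1.960 + 1.282)² × (0.16 + 0.16) / 0.10² = 336.2, so 337.
- Same test, null variance taken at 80% and 70%: (1.960 × √0.37 + 1.282 × √0.32)² / 0.10² = 367.5, so 368, which is within 1% of 370.

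The match with 368 is an inference. It is at least consistent with a one-sided 0.025 non-inferiority test, which is what the lower limit of a two-sided 95% interval delivers. The point below does not depend on how 370 was obtained.

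**Two illustrative results, 360 per arm.** Interval: d ± 1.96 × √[p₁(1 − p₁)/360 + p₂(1 − p₂)/360].
- Observed 80% against 80%: 0 ± 1.96 × √(0.32/360), or -5.8 to +5.8 points. Both limits are inside the margin. The literal rule withholds the claim; the intended rule grants it.
- Observed 75% against 80%: -5 ± 1.96 × √(0.3475/360), or -11.1 to +1.1 points. One limit is outside the margin. The literal rule grants the claim; the intended rule withholds it.

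**Probability of declaring non-inferiority.** Exact binomial enumeration, 360 per arm, Wald 95% interval, true abduction rate 80%. There are two literal readings: (a) the lower limit is beyond -10, whatever the upper limit does; (b) exactly one limit is beyond -10, so the interval straddles it.

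| True rate, active monitoring | Literal (a) | Literal (b) | Intended rule |
|---|---|---|---|
| 80% | 8.1% | 8.1% | 91.9% |
| 75% | 63.6% | 63.6% | 36.4% |
| 70% | 97.5% | 94.9% | 2.5% |

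A normal approximation checks the last column. At 80%, SE = √(0.32/360) = 0.0298 and Φ(0.10/0.0298 − 1.96) = Φ(1.39) ≈ 0.92. At 75%, SE = √(0.3475/360) = 0.0311 and Φ(0.05/0.0311 − 1.96) = Φ(−0.35) ≈ 0.36. At 70%, Φ(−1.96) = 0.025.

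**Sensitivity.** With 370 per arm, literal reading (a) gives 7.5%, 62.7% and 97.5%, and the intended rule gives 92.5%, 37.3% and 2.5%. If a limit outside either -10 or +10 counted, the literal figures at 360 per arm would be 16.3%, 63.8% and 97.5%. Every reading runs in the wrong direction across these three rates.

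**The case against.** The best defence is that nobody would apply the sentence literally. The hypothesis, the margin and the 70%-against-80% boundary are stated correctly, and the Discussion repeats the direction. The word *outside* could be read loosely as clear of the region of inferiority. This defence stands as far as intent goes. It does not rescue the sentence: the loose reading is not the natural one, the relevant side is still unnamed, and nothing else in the article states the rule correctly.

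The article may condense a fuller protocol or analysis plan, which could hold a properly worded rule. For that reason the missing sign convention alone would not be a finding. A criterion that is printed and reads backwards is different from one left for later.

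A reader might go further in three ways that the article does not support.
- That the trial tests the wrong hypothesis, or that the team would claim success at 70% against 80%. The sample size section and the Discussion say otherwise.
- That the comparison itself is undefined. The sentence just before the rule names the difference between the two arms.
- That literal success keeps rising the worse active monitoring performs. This holds only under reading (a). Under reading (b) it falls once intervals begin to lie wholly beyond the margin, so no figure below 70% is offered here.

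**Conclusion.** The point holds as a wording error in the primary decision rule. At the inferiority boundary the literal rule would declare non-inferiority in 95% to 97% of trials instead of 2.5%. With truly equal arms it would do so in about 8% instead of 92%. These figures assume 360 analysed per arm, a true abduction rate of 80% and Wald intervals. They describe what the sentence would do if followed, not what the team is likely to do. Because the intent is recoverable, the design, margin and sample size are not called into question. The sentence must still be corrected, since it is the only statement of how the primary question will be answered.

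**What to change.** Replace the sentence with:

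> Non-inferiority of active monitoring is concluded if the lower limit of the two-sided 95% CI for the difference in the proportion of normal hips at 12 months (active monitoring minus abduction treatment) is greater than -10 percentage points.

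This names the limit, the sign and the side of the margin. If the full protocol or analysis plan already has a correct rule, the article should be brought into line with it. The cost is one sentence. Data collection, sample size and participants are unaffected. The change should be documented before the outcome data are analysed.

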### Interventions

In the active monitoring group (± delayed treatment), infants will not wear an abduction device and will be evaluated every six weeks with ultrasound and physical examination until reaching one of the endpoints (Table 2, Fig. 1). In the abduction treatment group, infants will wear an abduction device (e.g. Pavlik harness) and will be evaluated every six weeks with ultrasound and physical examination until reaching one of the endpoints (Table 2, Fig. 1). The Pavlik harness will be applied in 90–100 degrees of flexion of both hips and maximal comfortable abduction. Standard check-up after 1 and/or 2 weeks is advised after the start of Pavlik treatment. All infants in both groups will be evaluated at the age of 12 and 24 months.

**Table 2 Tab2:** TRAM-Trial endpoints

Intervention	Endpoints	Treatment
Active monitoring	1. Hip normalization	Treatment will be discontinued as maximal results have been accomplished
	2. A total period of 18 weeks	Patients will receive treatment according to the standardized Dutch national protocol for usual care
	3. No improvement is observed on two consecutive imaging evaluations	
	4. Deterioration of the hip is observed with clinical examination or imaging. Deterioration for Graf type IIc is defined as worsening or not improving into Graf type IIb within 12 weeks	
	5. Inability to perform a reliable ultrasound evaluation because of progressive development of the ossific nucleus of the femoral head	Follow-up will be continued by obtaining radiographs
Abduction treatment	1. Hip normalization	Treatment with the dynamic abduction device will be discontinued as maximal results are accomplished
	2. No improvement is observed on two consecutive imaging evaluations	Patients will receive treatment according to the standardized Dutch national protocol for usual care
	3. Deterioration of the hip is observed with clinical examination or imaging	
	4. The infant is too strong for the dynamic abduction device	Abduction treatment will be continued using a static abduction device (e.g. CAMP device) until 1, 2 or 3 is accomplished
	5. Inability to perform a reliable ultrasound evaluation because of progressive development of the ossific nucleus of the femoral head	Follow-up will be continued by obtaining radiographs

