**Fig. 1 Fig1:**
[figure not shown]
TRAM-Trial flowchart

During baseline and follow-up evaluations, physical examination consists of weight measurements, asymmetric skin fold evaluation, knee height (Galeazzi test), degrees of hip abduction in flexion, and Barlow and Ortolani tests. At the age of 12 and 24 months, physical examination consists of degrees of hip abduction and leg length evaluation. Ultrasounds will be performed every 6 weeks according to the Graf method until hip normalization or technically restricted due to the appearance of the ossific nucleus of the femoral head. For the latter case, radiographs will be obtained in further follow-up. At the age of 12 and 24 months, pelvic radiographs will be performed according to a standardized protocol. Ultrasounds and radiographs will be assessed by local pediatric radiologists at the participating centers.

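### The time-to-normalisation event counts radiographs only at 12 and 24 months, so a hip that normalises on an interim radiograph is dated weeks to months late

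*Protocol article*

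**What the plan says.** Time to hip normalisation is a named secondary outcome (Abstract; Secondary outcomes). Statistical methods gives it a Kaplan-Meier analysis. The event rule reads "events defined as Graf I or acetabular index lower than 25 degrees at 12 months"; the same cut-off on the 24-month film also counts. On testing, the section says: "Differences in survival curves will be studied and tested for statistical significance with the Log Rank test".

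The imaging pathway is set out under Interventions.

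- **Ultrasound:** "Ultrasounds will be performed every 6 weeks according to the Graf method until hip normalization or technically restricted" by the appearance of the ossific nucleus.
- **After ultrasound is lost:** "For the latter case, radiographs will be obtained in further follow-up". The 12- and 24-month pelvic radiographs are listed separately, under their own standardised protocol.
- **Table 2, endpoint 5 in both arms:** "Inability to perform a reliable ultrasound evaluation because of progressive development of the ossific nucleus of the femoral head", with the consequence "Follow-up will be continued by obtaining radiographs".
- **Table 2, endpoint 1 in both arms:** hip normalisation, at which treatment stops.

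Data collection methods schedules visits "every six weeks (± 1 week) to collect physical examination data, ultrasonographic measurements, and data on compliance and complications, until one of the endpoints". It names radiograph measurements only for the 12- and 24-month visits. Under Data management, all ultrasounds and radiographs are pseudonymised and stored centrally.

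**The concern.** The event definition treats the two imaging methods differently. Graf I carries no time limit, so ultrasound normalisation is dated at the visit where it is seen. An acetabular index below 25 degrees counts only at two fixed ages. An infant who has lost reliable ultrasound can no longer be graded Graf I, so no event is possible before the 12-month film, whatever an interim film shows.

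The trial's clinical endpoint and its analysed event can then be months apart in the same infant: Table 2 can record normalisation and end treatment while the Kaplan-Meier analysis still carries the infant as not normalised. Time to normalisation would be overstated, with an artificial step at 12 months. If the two arms were affected unequally, part of any difference between the curves would come from dating and not from the hips.

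**Working it through.** The protocol gives no figure for this analysis, so there is none to reproduce. The check is how late an event is dated under the stated rule.

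**Inputs from the protocol**
- Entry at 10 to 16 weeks of age (Eligibility criteria).
- Visits every six weeks, ± 1 week; fixed visits at 12 and 24 months, ± 1 month (Data collection methods).
- A +36-week visit only for infants included at 10 weeks (Table 3, footnote 3).

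**Assumption.** Interim radiographs take the place of ultrasound at the six-weekly visits. The text does not give their frequency, and Table 3 itself is not reproduced in the copy reviewed.

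**Step 1: delay for one infant**

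Delay = age at the 12-month film − age at the interim film, with 12 months = 365.25 / 7 = 52.2 weeks and 4.348 weeks per month.

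| Age at normal interim film (weeks) | Example | Delay (weeks) | Delay (months) |
|---|---|---|---|
| 16 | entry 10, visit +6 | 52.2 − 16 = 36.2 | 8.3 |
| 28 | entry 10, visit +18 | 52.2 − 28 = 24.2 | 5.6 |
| 34 | entry 16, visit +18 | 52.2 − 34 = 18.2 | 4.2 |
| 40 | entry 16, visit +24 | 52.2 − 40 = 12.2 | 2.8 |
| 46 | entry 10, visit +36 | 52.2 − 46 = 6.2 | 1.4 |

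The nominal range is 6 to 36 weeks. With the visit windows the extremes are about 0.2 and 9.6 months. The long end requires ultrasound to be lost by the first follow-up visit.

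These delays assume an index below 25 degrees at 12 months. If it is 25 degrees or more, the event moves to 24 months, or the infant is censored.

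**Step 2: effect on the curve**

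The share of infants affected, f, is not in the documents, so a range is shown. Take entry at 13 weeks. Ultrasound normalisers are seen at +6 or +12 weeks and dated correctly. Interim-film normalisers are seen in equal numbers at +18 and +24 weeks, mean +21. The 12-month film falls at 52.2 − 13 = +39.2 weeks, so each interim-film normaliser is on average 39.2 − 21 = 18.2 weeks late.

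Shift in mean recorded time = f × 18.2 weeks.

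| f | Shift in mean (weeks) | Recorded as normal by +24 weeks (true: 100%) |
|---|---|---|
| 10% | 1.8 | 90% |
| 30% | 5.5 | 70% |
| 50% | 9.1 | 50% |

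**Step 3: comparison of arms**

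The log-rank test was simulated with identical true curves in both arms, 400 infants per arm, and an exponential time giving 80% normal by week 39. Infants on the full schedule could have events at weeks 6, 12, 18, 24, 30, 39 and 91. Uncountable infants had no possible event between weeks 18 and 39.

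| Uncountable, active monitoring v abduction | Two-sided 5% test rejects |
|---|---|
| 50% v 50%, or 100% v 100% | about 5% |
| 60% v 40% | about 6% |
| 50% v 0% | about 13% |
| 100% v 0% | about 45% |

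When both arms are affected alike, the test holds its level. It fails clearly only when the arms are affected very unequally.

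**The case against.** **Stronger readings the protocol does not support**

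*A false difference between arms is likely.* A reader might infer this because active monitoring has an 18-week endpoint leading to usual care, abduction has no time limit, and six-weekly collection runs only until an endpoint. If every abduction infant is also given a +36-week visit and every monitored infant loses all countable events between weeks 18 and 39, the simulated rejection rate is 65 to 68%. That scenario is not documented:
- The +36-week visit is limited to infants included at 10 weeks, whereas a 12-month film at week 39 implies entry at 13 weeks.
- The ultrasound rule has no 18-week stop and does not distinguish arms.
- Abduction infants also leave through no improvement or deterioration.
- Nothing excludes a Graf I result obtained in usual care.

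*About 28% of infants are dated 12 weeks late.* Under the exponential model, exp(−18 × 0.0413) − 0.20 = 0.28 normalise between weeks 18 and 39, on average 12 weeks before week 39. This is a ceiling on the share, because those who reach Graf I on ultrasound are dated correctly. Also, 12 weeks runs from true onset; measured from the next six-weekly visit the extra delay is about 8 to 9 weeks.

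**Other objections**

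*Limiting radiographic events to the two fixed ages may be deliberate.* The index cut-off and the standardised film protocol are stated only for those ages. This has weight: the protocol contains no interim radiographic criterion that could simply be applied, so one must be set. It does not remove the mismatch with Table 2, which makes hip normalisation an endpoint during follow-up while continuing that follow-up by radiograph.

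*Event-dating detail belongs in an SAP, which is not at hand, and Kaplan-Meier with log-rank on common visits is standard.* The second part stands, so interval-censored analysis is a refinement and not a correction. The first does not: the event rule is written out in full, and it conflicts with the imaging pathway in the same article.

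**Conclusion.** The point holds for the event definition. Followed as written, the rule dates an infant who normalises on an interim radiograph at the 12-month film or later, about 6 to 36 weeks late at nominal six-weekly visits. It rests on the protocol's own text and on the assumption that interim films follow the six-weekly schedule. Endpoint 5 is itself one of the endpoints that closes six-weekly trial collection, so even that frequency is uncertain.

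The total bias cannot be sized, because neither the number of infants who lose ultrasound before Graf I nor the age at which this happens is given. It moves the level of both curves. It distorts the log-rank comparison only if the share or timing of lost ultrasound, or the schedule after an endpoint, differs between arms. The matter is confined to a secondary outcome; the primary outcome at 12 months is untouched. It should be corrected before the data are analysed.

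**What to change.** 1. Define the event as the first imaging, ultrasound or radiograph, at any visit up to 24 months, that shows hip normalisation, and date it at that examination.
2. Have the trial team set in advance the radiographic criterion for interim films, and reconcile it with the hip-normalisation endpoint in Table 2. The choice of criterion is theirs.
3. Record in the case report form the interim radiograph measurement and the dates of the last non-normal and first normal imaging.
4. Keep the Kaplan-Meier and log-rank analysis, and add an interval-censored sensitivity analysis (for example a Turnbull curve with an interval-censored log-rank test), since normalisation is known only to lie between two visits.

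The cost is a few data fields, reading measurements from films already stored centrally, and a little more analysis work, possibly in other software. No new visit, image or participant is needed. Results from usual-care imaging after an endpoint may have to be requested, because the protocol does not say that they are collected.
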